Therefore, we developed a novel prognostic model using data from the *diamond* cohort study [39] to predict depressive symptom severity at three months [38]. It comprises 17 items assessing depressive symptom severity at baseline as measured by the Patient Health Questionnaire-9 (PHQ-9) [40]: sex; current anxiety; history of depression; presence of chronic illness affecting daily functioning; self-rated health; living alone; and perceived ability to manage on available income. Based on an individual’s score, he or she is stratified into one of three groups based on predicted depressive symptom scores at three months; namely, minimal/mild (those predicted to have a PHQ score of ≤ 10 at three months), moderate (PHQ > 10 and < 13), and severe (≥13). Cutoffs for the three groups were established during the development of the *diamond* CPT and are explained in full elsewhere [38]. In the intervention being tested in the current study, individuals are then:Presented with feedback reflecting their responses to the CPT;Provided an opportunity to set priorities and reflect on motivation to change; andPresented with an evidence-based treatment recommendation matched to group classification.

The presentation of feedback and treatment recommendation was informed by the principles of motivational interviewing [41] and an iterative development process employing user-centered design principles to ensure the information is presented in a way that is meaningful and engaging for participants [42].

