### Assignment of interventions

#### Allocation

Consent and baseline measures will be collected prior to randomization to minimize reporting and selection bias. When the individual has completed the *diamond* CPT, he or she will be randomly assigned in a 1:1 ratio to the intervention or comparison arm. Randomization will be stratified by general practice and depressive symptom severity group. The allocation sequence will be computer-generated sequentially within stratum using a biased-coin algorithm [64] embedded within the Target-D website which is housed on the secure National eResearch Collaboration Tools and Resources (Nectar) cloud which provides computing infrastructure to Australian researchers. Using restricted randomization within the stratum ensures that number of individuals is balanced between study arms within stratum and the stratification factors will be balanced in each study arm. The randomization will be triggered automatically within the Target-D website, after a participant has completed baseline measurements and the *diamond* CPT, thus ensuring allocation concealment.

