#### Blinding

Due to the nature of the intervention, participants cannot be blinded to their treatment allocation. However, GPs will not be notified of their patients’ allocation to either intervention or comparison arm. No emergency unblinding of GPs is anticipated, including in the case of the research team alerting the GP to patient suicidality. As outcome assessment is conducted online, no blinding of outcome assessors is required. All study analyses will be conducted by a statistician blind to participants’ allocation; study arm allocation will be coded as A or B, with the code for the study arm revealed only after data are analyzed.

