### Statistical methods

Descriptive statistics will be used to compare participant characteristics between the study arms, in total and stratified according to depressive symptom severity group. Linear mixed-effects model using restricted maximum likelihood with random intercepts for individuals will be used to estimate the difference in mean outcome between study arms at three and 12 months. All regression models will adjust for baseline outcome measure (where appropriate), stratification factors (practice, depressive symptom severity group) and time (baseline, three and 12 months), with a two-way interaction between study arm and time except baseline where means in the study arms will be constrained to be equal. Baseline variables strongly associated with the outcome that are found to be imbalanced between the study arms will also be considered for adjustment in the regression analyses. Estimated intervention effects will be reported as the difference in the means of the outcome between study arms (intervention-comparison), with 95% confidence intervals and *p* values. Similar regression analyses will also be used to compare the outcomes between intervention and comparison arms separately for each of the three depressive symptom severity groups. In a secondary analysis, we will investigate the intervention effect on individuals who would comply with their assigned treatment using a complier average casual effect (CACE) analysis [76]. A detailed analysis plan will be developed for the secondary and sensitivity analyses. All analyses will be performed using Stata 13.0 [77].

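### Covariates can enter the primary model according to observed baseline imbalance, while the continuous predicted score available before randomisation is used only as a three-level group

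*Protocol article*

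**What the plan says.** The Statistical methods section of the protocol article describes one family of linear mixed models for the three- and 12-month contrasts. On covariates it states: "All regression models will adjust for baseline outcome measure (where appropriate), stratification factors (practice, depressive symptom severity group", and it continues with time and an arm-by-time interaction, the arm means being held equal at baseline. The next sentence adds the rule at issue: "Baseline variables strongly associated with the outcome that are found to be imbalanced between the study arms will also be considered for adjustment". No candidate variable, strength of association or size of imbalance is given, and qualifying variables need only be considered. The same section says "A detailed analysis plan will be developed for the secondary and sensitivity analyses", which does not name the primary model.

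Under Background and rationale, participants are "stratified into one of three groups based on predicted depressive symptom scores at three months", with cut points at 10 and 13. Besides baseline PHQ-9 and sex, the tool uses "current anxiety; history of depression; presence of chronic illness affecting daily functioning; self-rated health; living alone; and perceived ability to manage on available income". Trial design says that both arms complete the tool. Allocation gives the timing: "The randomization will be triggered automatically within the Target-D website, after a participant has completed baseline measurements and the" prediction tool. The continuous predicted score appears in no analysis model.

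Under Blinding, "study arm allocation will be coded as A or B, with the code for the study arm revealed only after data are analyzed".

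**The concern.** Two separate points meet in this paragraph.

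**The rule.** After concealed randomisation any baseline imbalance is due to chance, and a prognostic covariate improves precision whether or not it is imbalanced. Imbalance is therefore a poor criterion for choosing covariates. Because it is assessed in the trial data, and because the decision is left open even when both conditions are met, the primary estimate and p value can turn on a choice made after data are available.

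**The unused score.** The trial holds, for every randomised participant, a baseline quantity built to predict the primary outcome measure at the primary time point. Cutting it into three groups discards the variation within each group. Baseline PHQ-9 recovers part of this. The other predictors enter only through the group, and in the per-group analyses, where the group is constant, they do not enter at all.

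**Working it through.** **1. The plan's own figure.** Inputs from Sample size: difference 1.35 points (0.2 SD), SD 6.75, 528 per arm, two-sided 5%, 90% power.
- SE = 6.75 × √(2/528) = 0.415.
- Power = Φ(1.35/0.415 − 1.96) = 90.1%.
- Required n is 526 per arm against 528 stated, and 1056/0.8 = 1320.

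The primary figure reproduces.

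**2. What the imbalance rule does.** Simulation of 400,000 trials with 528 per arm and one covariate explaining a share R² of outcome variance. The document gives no R², so 0.05 to 0.30 is an assumption. Imbalance is taken as p < 0.05 for the covariate between arms, also an assumption because the plan sets no threshold. All figures are percentages.

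| R² | Type I, rule applied mechanically | Type I, more favourable model chosen | Power, rule | Power, always adjust |
|---|---|---|---|---|
| 0.05 | 4.9 | 6.0 | 90.5 | 91.6 |
| 0.10 | 4.7 | 6.5 | 90.5 | 92.9 |
| 0.20 | 4.5 | 7.1 | 90.9 | 95.4 |
| 0.30 | 4.2 | 7.6 | 91.3 | 97.3 |

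Always adjusting holds type I error at 5.0%. The power columns start from the unadjusted SD of 6.75 and give no credit for the planned baseline adjustment. They show the direction of the loss, not its size in this trial. The type I columns do not depend on the SD.

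**3. What the continuous score could add.** A simulated ANCOVA at three months already contained baseline PHQ-9, severity group and practice. It assumed that the tool's non-PHQ items carry c = 1.5 PHQ-9 points per SD.
- SE without the score 0.297, with it 0.287.
- Variance ratio = (0.287/0.297)² = 0.934, a reduction of about 7%.
- 1056/0.934 ≈ 1131, equivalent to about 75 more analysed participants.

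Approximate scaling, 0.75 × c²/(c² + 23), where 0.75 and 23 are also assumptions from that simulation:
- c = 1: 0.75 × 1/24 = 3%.
- c = 2: 0.75 × 4/27 = 11%.

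**4. What that means for power.** At a true difference of 1.35:
- Without the score: Φ(1.35/0.297 − 1.96) = Φ(2.59) = 99.5%.
- With it: Φ(1.35/0.287 − 1.96) = Φ(2.74) = 99.7%.

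In that simulation the planned covariates alone already bring the variance down to (0.297/0.415)² ≈ 0.51 of the unadjusted value, so little power is left to gain overall.

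**5. The moderate group.** Its band of predicted scores is under 3 points wide. If scores are roughly uniform within it, their SD is at most 3/√12 = 0.87 and their variance 0.75. Against the assumed residual variance of 23, that is about 3%.

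**The case against.** The core covariates are fixed, the extra ones must also be strongly prognostic, and the analyst is blinded. The text does not say that association will be judged from trial outcomes; it could come from the development cohort. Followed mechanically the rule is conservative, and inflation needs someone to pick the better-looking result, which the plan does not propose. Covariate lists and thresholds are often left to an analysis plan. The continuous score is a preference: baseline PHQ-9 is already in the model, and the 7% comes from assumed inputs and an ANCOVA, not the planned mixed model.

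Much of this stands. A reader might infer that the plan produces an inflated type I error, but the document supports only that it leaves room for one. A reader might also infer that leaving out the score biases the estimate or costs substantial power; it does neither on these figures. Nor can it be said that the moderate and severe groups gain most: that was not computed, and the narrow moderate band makes it doubtful there.

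Two parts of the objection fail. The imbalance criterion is stated, not merely left unspecified, and the detailed plan is promised only for secondary and sensitivity analyses. A sharper threshold would not turn imbalance into a good criterion. And A/B coding conceals which arm is which, but not which model gives the larger difference or the smaller p value.

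**Conclusion.** The point holds in limited form. The primary covariate set is open to change according to observed imbalance. Followed mechanically, the rule is slightly conservative (4.9% to 4.2%) and less precise than always adjusting. Used with discretion, it could raise type I error to 6.0% to 7.6%, an upper bound for one covariate with an assumed R² of 0.05 to 0.30.

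Using the predicted score only as a group is a modest inefficiency. Its size cannot be fixed from the document: roughly 3% to 11% of variance under assumed values, not demonstrated for the constrained mixed model, and worth about 0.2 percentage points of overall power in the one simulated case. The change is worthwhile because it costs almost nothing and closes the primary model in advance, not because the trial is at risk without it.

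**What to change.** Remove the imbalance criterion from the primary analysis, or keep it only as a labelled sensitivity analysis. State the primary covariates in advance: baseline PHQ-9, practice, severity group and the continuous predicted three-month score. Baseline is a time point in the constrained model and baseline PHQ-9 is a component of the score, so the score's relation to the outcome will differ by time; enter it with a score-by-time term. Use the same set without severity group in the three per-group analyses.

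No new data are needed, because every participant completes the tool before allocation. The cost is a revised paragraph and a few extra model parameters. The article reports recruitment as ongoing at submission, so the change could be recorded before analysis.

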#### Missing data

Analyses will use an ITT approach, where participants will be analyzed in the study arm to which they were allocated [78]. In the first instance, we will implement strategies to minimize the missing outcome data, including the participant retention strategies outlined above. Reasons participants are lost to follow-up will be recorded. Sensitivity analysis will be used to assess the robustness of the missing data assumption.

#### Cost-effectiveness and cost-utility analysis

Incremental cost-effectiveness ratios (ICERs) will be determined (cost of intervention – costs of comparison/outcome of intervention – outcome of comparison) using the AQoL-8D to determine QALYs. ICERs using other important study outcomes (such as cost per remitted case) will also be determined. Variation will be determined by bootstrap and regression analyses and results presented in cost-effectiveness planes and acceptability curves. Sensitivity analyses will also be used to determine the impact of important study parameters (such as unit cost price variation). Dependent on trial results, modeling may also be used to extrapolate beyond the trial time horizon.

### Monitoring

The Target-D study will be monitored by the Steering Committee (SC) and a Data Monitoring Committee (DMC). The SC will comprise all named investigators and the project manager and will be led by the Chief Investigator. The SC will have biannual meetings to monitor recruitment progress, troubleshoot any areas of concern, ensure that the project is being conducted according to protocol, and identify additional training or support required by the research staff to facilitate the smooth running of the trial.

The DMC will comprise at least three members and be led by [name], an experienced researcher independent of the research team. Collectively, DMC members will have clinical, research, and statistical expertise across primary care and mental health. Members of the DMC will be provided with a Charter outlining their scope of responsibilities (Additional file 5). The DMC will meet biannually to monitor trial processes and progress, and review complaints, harms, and adverse events. Adverse events may be serious or otherwise; the former are defined as those which “might be significant enough to lead to important changes in the way the [intervention] is developed” [79]. In light of the fact that the interventions used in the study are evidence-based, and all participants are linked in with health services, routine data collection will assess adverse events and no interim analyses or auditing are planned. All adverse events will be recorded (including relation to study, severity, potential for the event to have been anticipated, and action taken) and reported to the DMC. Serious adverse events will also be reported to the University ethics committee.

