#### Comparison arm

Participants randomized to the comparison arm will access health services as usual. The choice of “usual care” as a comparator was made as the study aims to determine the extent to which the intervention improves (or worsens) patient outcomes relative to standard practice [56]. Participants in this arm will also receive some non-therapeutic attention from Target-D to control for any effect of contact with the study team following completion of the *diamond* CPT; thus, this study arm is referred to as “Usual care plus Target-D” or UC+. UC+ participants will be blinded to their depressive symptom severity group allocation and will not receive a tailored treatment recommendation. Instead, they will see a screen on the Target-D website advising them that they will be asked to provide feedback on: (1) their opinions on research in primary care; and (2) how they normally manage their emotional health and wellbeing. Similar to the procedure for intervention participants, those in the usual care arm will be contacted by phone by an RA within one week of *diamond* CPT completion. The RA will reiterate the importance of the participant’s involvement in the study, ask a series of structured questions about the participant’s views on research and the involvement of their general practice in research, and advise the participant that he or she will be contacted via email in 12 weeks.

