#### Modifications

The nature of the study interventions is such that no substantive modifications are anticipated. Patients in the minimal/mild and moderate groups may discontinue using the online program at any time and treatment for those in the severe group may be discontinued at patient request.

If any participant indicates high levels of suicidal ideation during contact with a member of the study team (as indicated by a response of “nearly every day” to question 9 on the PHQ-9: “thoughts that you would be better off dead or of hurting yourself in some way”), regardless of study arm allocation, a standardized suicidal ideation assessment used previously by the study team will be administered and the patient’s GP alerted. This will be reported as an adverse event but is unlikely to result in treatment discontinuation or modification. The assessment will determine if the adverse event was related directly to the intervention or other circumstances not intervention related.

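### A serious adverse event is defined by its bearing on the intervention, not by the patient's outcome, so a death or suicide attempt need not be classed as serious or reach the ethics committee

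*Protocol article*

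**What the plan says.** The Monitoring section of the protocol article divides adverse events into serious and other. Serious events are those that "might be significant enough to lead to important changes in the way the [intervention] is developed". The wording is taken from a cited source, and no list of qualifying patient outcomes goes with it.

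The same section then sets out what happens to events:

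- Recording: "All adverse events will be recorded (including relation to study, severity, potential for the event to have been anticipated, and action taken"), with all of them reported to the DMC.
- Review: "The DMC will meet biannually to monitor trial processes and progress, and review complaints, harms, and adverse events".
- Ethics committee: "Serious adverse events will also be reported to the University ethics committee".
- Other oversight: "routine data collection will assess adverse events and no interim analyses or auditing are planned".

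The Modifications section covers high suicidal ideation in either arm. It provides for a standardized assessment, an alert to the GP and reporting as an adverse event. On cause it says: "The assessment will determine if the adverse event was related directly to the intervention or other circumstances not intervention related". It does not say whether such an event is serious, and it does not mention attempts or deaths. Ethics and dissemination sends substantive protocol changes to the ethics committee but gives no further route for adverse events.

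**The concern.** A seriousness category should pick out the events that are gravest for the patient, so that someone outside the trial team hears of them. The stated test asks something else: what the event implies for the future of the intervention. Two equally grave events can therefore receive different labels, depending on whether anyone thinks the intervention had a part in them.

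This matters because the label carries a reporting duty. The ethics committee is told of serious events and, on the text shown, of no others. Participants are recruited for depressive symptoms and the protocol itself anticipates suicidality, so suicide attempts and deaths are foreseeable. What is at stake is the completeness of safety reporting to the ethics committee. The estimate of the treatment effect is not at stake.

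**Working it through.** No arithmetic applies: the point concerns a definition and the route attached to it. The check was to look for any other definition of serious, or any other adverse-event route to the ethics committee, in Comparison arm, Modifications, Blinding, Monitoring, and Ethics and dissemination. There is none. The stated rule was then applied to four cases.

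1. **Suicide attempt in the intervention arm, judged related to the intervention.** It plainly might change how the intervention is developed. It is serious and goes to both the DMC and the ethics committee. The rule works.
2. **Death in either arm, judged to come from circumstances unrelated to the intervention.** Such a death gives little reason to develop the intervention differently, so the test is not clearly met. It goes to the DMC. The text does not require a report to the ethics committee.
3. **Hospital admission judged unrelated, in either arm.** The reasoning and the result are the same as in case 2.
4. **Suicide attempt in UC+.** This participant received no feedback and no matched treatment recommendation (Trial design, Comparison arm), which argues against the test being met. But the participant did complete the prediction tool and was classified by it. An attempt by someone predicted to have minimal or mild symptoms could bear on the tool and so might meet the test. The label is left to judgement.

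Cases 1 and 4 can be the same event for the patient, with a report to the ethics committee required in one and discretionary in the other. Cases 2 and 3 show the gap most clearly, because judged cause in effect decides seriousness.

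The definition does not need to do that work. Monitoring already records relation to the study and severity as separate items for every event, and Modifications calls for a judgement of relatedness when high ideation is found. Neither item is used to define serious.

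**The case against.** The best case for the plan has five parts.

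**The article is a condensed account.** The definition is a fragment of a cited source, and the DMC Charter (Additional file 5) and the protocol approved by the ethics committee are not shown. Any of these could list qualifying outcomes or add a route. This stands as a limit on how much can be concluded. It does not remove the point, because the article does not leave the definition to another document: it states one and attaches a duty to it.

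**The wording is permissive and names neither arm nor cause.** This also stands. A death can be classed as serious under it. The text does not require that it be.

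**Events are not lost.** All adverse events in both arms go to a DMC led by someone independent of the research team, and the GP is alerted to high suicidal ideation whichever arm the patient is in. This stands, and it confines the gap to classification and to what the ethics committee hears.

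**Lighter monitoring is justified.** The section points to treatments with existing evidence and to participants' links with health services. That supports having no interim analyses. It is not a reason to define seriousness without reference to the patient.

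**A new label detects nothing.** This is correct. The change affects classification and routing only; it does not improve the capture of deaths, attempts or admissions.

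A reader might also infer three stronger things that the documents do not support:

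- That UC+ events are excluded from the serious category. They are not; case 4 could go either way.
- That the harm comparison between arms is biased, because "the study aims to determine the extent to which the intervention improves (or worsens) patient outcomes relative to standard practice". That sentence explains the choice of comparator, and no between-arm comparison of serious events is planned.
- That a grave event waits for the next twice-yearly DMC meeting. The article says when the DMC meets and that events are reported to it, but does not tie the reporting to the meetings.

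**Conclusion.** The point holds in a limited form. The one stated definition of a serious adverse event contains no patient-outcome criterion, and it alone decides which events have a stated route to the ethics committee. A death, suicide attempt or other life-threatening event therefore need not be classed as serious or reported there. This is clearest when the event is judged unrelated, and possible when it occurs in UC+.

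The number of events affected cannot be derived. The article gives no rate for deaths, attempts or admissions. Even a rate would show only how often such events occur, not how often one would be labelled non-serious. The primary and secondary efficacy results are untouched.

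The conclusion assumes that the Charter and the ethics committee's own rules do not already supply an outcome-based definition or a separate route. If they do, the article's sentence only needs to be brought into line with them. The change should be made because it is specific and cheap; nothing here threatens the trial's findings.

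**What to change.** Replace the definition in Monitoring with one based on the event's outcome: a serious adverse event is a death, a life-threatening event (including a suicide attempt) or a hospital admission, in either arm and whatever its judged cause. Keep relation to the study as the separate item it already is. State that serious events are reported to the University ethics committee under that committee's own rules, which can also settle which events it wants to see individually. The clinical response to suicidal ideation, the design and the analysis stay as they are.

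The cost is more classification and reporting, mainly because hospital admissions would now count. As a scale only, each 1% of the planned 1,320 participants with a qualifying event is 1,320 × 0.01 = 13.2 people across both arms. Some of their events would have been classed as serious anyway, and the committee's rules may call for fewer individual reports. Recruitment was under way when the article was submitted (Trial status), so the change would also need an ethics amendment before it takes effect.
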